#### **10.3. Lack of Efficacy**

“Lack of efficacy” per se will not be reported as an AE. The signs and symptoms or clinical sequelae resulting from lack of efficacy will be reported if they fulfil the AE or SAE definition (including clarifications).

#### **10.4. Clinical Laboratory Abnormalities and Other Abnormal Assessments as AEs and SAEs**

Abnormal laboratory findings (e.g., clinical chemistry, hematology, urinalysis) or other abnormal assessments (e.g., ECGs, chest x-ray) that are judged by the investigator as **clinically significant** will be recorded as AEs or SAEs if they meet the definition of an AE, as defined in Section 10.1 ("Definition of an AE"), or SAE, as defined in Section 10.2 ("Definition of a SAE"). Clinically significant abnormal laboratory findings or other abnormal assessments that are detected during the study or are present at baseline and significantly worsen following the start of the study will be reported as AEs or SAEs. However, clinically significant abnormal laboratory findings or other abnormal assessments that are associated with the disease being studied, unless judged by the investigator as more severe than expected for the patient's condition, or that are present or detected at the start of the study and do not worsen, will **not** be reported as AEs or SAEs.

The investigator will exercise his or her medical and scientific judgement in deciding whether an abnormal laboratory finding or other abnormal assessment is clinically significant.

### **10.5. Time Period, Frequency, and Method of Detecting AEs and SAEs**

Any pre-existing conditions or signs and/or symptoms present in a patient prior to the start of the study (i.e. before informed consent) should be recorded in the Medical/Surgical History section within the CRF.

In order to fulfil international reporting obligations, SAEs that are related to study participation (e.g. procedures, invasive tests, change from existing therapy) or are related to a concomitant medication will be collected and recorded from the time the patient consents to participate in the study until he/she is withdrawn or completes.

Any medical occurrences which occur after informed consent is obtained but prior to starting active or randomised treatment will be documented on the Baseline Signs & Symptoms section within the CRF.

All AEs occurring after administration of the first dose of study medication and on or before the final visit must be reported on the Adverse Event form in the CRF. All AEs must be recorded irrespective of whether they are considered drug related.

At each visit/assessment in the period defined above, AEs will be evaluated by the investigator and recorded in the appropriate AE/Serious AE section of the CRF.

Any AEs already documented at a previous assessment and designated as ongoing, should be reviewed at subsequent visits as necessary. If these have resolved, the documentation in the CRF should be completed. If an AE changes in intensity/frequency then this should be recorded as a separate event (i.e. a new record started).

As a consistent method of soliciting AEs, the patient should be asked a non-leading question such as:

"Have you felt different in any way since starting the new treatment/or since the last visit?"

or

"How do you feel?"

### **10.6. Recording of AEs and SAEs**

When an AE/SAE occurs, it is the responsibility of the investigator to review all documentation (e.g., hospital progress notes, laboratory, and diagnostics reports) relative to the event. The investigator will then record all relevant information regarding an AE/SAE on the CRF. It is not acceptable for the investigator to send photocopies of the

patient's medical records to GSK in lieu of completion of the appropriate AE/SAE CRF pages. However, there may be instances when copies of medical records for certain cases are requested by GSK. In this instance, all patient identifiers will be blinded on the copies of the medical records prior to submission to GSK.

The investigator will attempt to establish a diagnosis of the event based on signs, symptoms, and/or other clinical information. In such cases, the diagnosis should be documented as the AE/SAE and not the individual signs/symptoms.

## **10.7. Evaluating AEs and SAEs**

### **10.7.1. Assessment of Intensity**

The investigator will make an assessment of intensity for each AE and SAE reported during the study. The assessment will be based on the investigator's clinical judgement. The intensity of each AE and SAE recorded in the CRF should be assigned to one of the following categories:

**Mild:** An event that is easily tolerated by the patient, causing minimal discomfort and not interfering with everyday activities.

**Moderate:** An event that is sufficiently discomforting to interfere with normal everyday activities.

**Severe:** An event that prevents normal everyday activities.

An AE that is assessed as severe should not be confused with a SAE. Severity is a category utilized for rating the intensity of an event; and both AEs and SAEs can be assessed as severe. An event is defined as 'serious' when it meets one of the pre-defined outcomes as described in Section 10.2, "Definition of a SAE".

### **10.7.2. Assessment of Causality**

The investigator is obligated to assess the relationship between investigational product and the occurrence of each AE/SAE. The investigator will use clinical judgement to determine the relationship. Alternative causes, such as natural history of the underlying diseases, concomitant therapy, other risk factors, and the temporal relationship of the event to the investigational product will be considered and investigated. The investigator will also consult the CIB/IB and/or Product Information, for marketed products, in the determination of his/her assessment.

There may be situations when an SAE has occurred and the investigator has minimal information to include in the initial report to GSK. However, it is very important that the investigator always make an assessment of causality for every event prior to transmission of the SAE CRF to GSK. The investigator may change his/her opinion of causality in light of follow-up information, amending the SAE CRF accordingly. The causality assessment is one of the criteria used when determining regulatory reporting requirements.

The investigator will provide the assessment of causality as per instructions on the SAE form in the CRF.

## **10.8. Follow-up of AEs and SAEs**

After the initial AE/SAE report, the investigator is required to proactively follow each patient and provide further information to GSK on the patient's condition.

All AEs and SAEs documented at a previous visit/contact and are designated as ongoing, will be reviewed at subsequent visits/contacts.

All AEs and SAEs will be followed until resolution, until the condition stabilizes, until the event is otherwise explained, or until the patient is lost to follow-up. Once resolved, the appropriate AE/SAE CRF page(s) will be updated. The investigator will ensure that follow-up includes any supplemental investigations as may be indicated to elucidate the nature and/or causality of the AE or SAE. This may include additional laboratory tests or investigations, histopathological examinations, or consultation with other health care professionals.

GSK may request that the investigator perform or arrange for the conduct of supplemental measurements and/or evaluations to elucidate as fully as possible the nature and/or causality of the AE or SAE. The investigator is obligated to assist. If a patient dies during participation in the study or during a recognized follow-up period, GSK will be provided with a copy of any post-mortem findings, including histopathology.

New or updated information will be recorded on the originally completed "SAE" CRF, with all changes signed and dated by the investigator. The updated SAE CRF should be resent to GSK within the time frames outlined in Section 10.9.

## **10.9. Prompt Reporting of SAEs to GSK**

SAEs will be reported promptly to GSK as described in the following table once the investigator determines that the event meets the protocol definition of an SAE.

### **10.9.1. Timeframes for Submitting SAE Reports to GSK**

|             | Initial SAE Reports |                 | Follow-up Information on a Previously Reported SAE |                         |
|-------------|---------------------|-----------------|----------------------------------------------------|-------------------------|
| Type of SAE | Time Frame          | Documents       | Time Frame                                         | Documents               |
| All SAEs    | 24 hrs              | "SAE" CRF pages | 24 hrs                                             | Updated "SAE" CRF pages |

### **10.9.2. Completion and Transmission of the SAE Reports**

Once an investigator becomes aware that an SAE has occurred in a study patient, she/he will report the information to GSK within 24 hours as outlined in Section 10.9. "Prompt Reporting of SAEs to GSK". The SAE CRF will always be completed as thoroughly as possible with all available details of the event, signed by the investigator (or designee), and forwarded to GSK within the designated time frames. If the investigator does not have all information regarding an SAE, he/she will not wait to receive additional information before notifying GSK of the event and completing the form. The form will be updated when additional information is received.

The investigator will always provide an assessment of causality at the time of the initial report as described in Section 10.7.2 "Assessment of Causality".

Facsimile transmission of the "SAE" CRF is the preferred method to transmit this information to the project contact for SAE receipt. In rare circumstances and in the absence of facsimile equipment, notification by telephone is acceptable, with a copy of the "SAE" CRF sent by overnight mail. Initial notification via the telephone does not replace the need for the investigator to complete and sign the SAE CRF within the time frames outlined in Section 10.9, "Prompt Reporting of SAEs to GSK".

GSK will provide a list of project contacts for SAE receipt, fax numbers, telephone numbers, and mailing addresses.

The following pages of the CRF must accompany the SAE forms that are forwarded to GSK: "Demography", "Medical History", "Concomitant Medications", "Study Medication Records", and "Form D" (if applicable).

### **10.10. Regulatory Reporting Requirements for SAEs**

The investigator will promptly report all SAEs to GSK in accordance with the procedures detailed in Section 10.9, "Prompt Reporting of SAEs to GSK." GSK has a legal responsibility to notify, as appropriate, both the local regulatory authority and other regulatory agencies about the safety of a product under clinical investigation. Prompt notification of SAEs by the investigator to the appropriate project contact for SAE receipt is essential so that legal obligations and ethical responsibilities towards the safety of other patients are met.

The investigator, or responsible person according to local requirements, will comply with the applicable local regulatory requirements related to the reporting of SAEs to regulatory authorities and the Institutional Review Board (IRB)/Independent Ethics Committee (IEC).

Expedited Investigator Safety Reports (EISR) are prepared according to GSK policy and are forwarded to investigators as necessary. An EISR is prepared for a SAE that is both attributable to investigational product and unexpected. The purpose of the EISR is to fulfil specific regulatory and Good Clinical Practice (GCP) requirements, regarding the product under investigation.

An investigator who receives an EISR describing a SAE or other specific safety information from GSK will file it with the Investigator Brochure and will notify the IRB or IEC, if appropriate according to local requirements.

### **10.11. Post-Study AEs and SAEs**

A post-study AE/SAE is defined as any event that occurs outside of the AE/SAE detection period defined in Section 10.5, “Time Period, Frequency, and Method of Detecting AEs and SAEs”, of the protocol.

Investigators are not obligated to actively seek AEs or SAEs in former study participants. However, if the investigator learns of any SAE, including a death, at any time after a patient has been discharged from the study, and he/she considers the event reasonably related to the investigational product, the investigator will promptly notify GSK.

### **10.12. SAEs Related to Study Participation**

An SAE considered related to study participation (e.g., procedures, invasive tests, a change in existing therapy), even if it occurs during the pre- or post-treatment period, will be reported promptly to GSK (see Section 10.9, "Prompt Reporting of SAEs to GSK").

## **11. DATA ANALYSIS AND STATISTICAL CONSIDERATIONS**

### **11.1. Hypotheses**

The primary objective is to show that SB-480848 shows superiority versus placebo in lowering carotid plaque Lp-PLA2 activity levels. As carotid plaque can only be obtained following surgery the null hypothesis to be tested is that there is no difference in plaque Lp-PLA2 activity levels between placebo and active groups following 14 (+/- 4) days of dosing. The alternative hypothesis is that there is a difference between placebo and one or more active dose levels. Testing will be two-sided.

### **11.2. Treatment Comparisons of Interest**

#### **11.2.1. Primary Comparisons of Interest**

The primary objective of the study will be assessed by tests of hypotheses. The value of carotid plaque Lp-PLA2 activity will be compared between placebo and each active group. The primary analysis will be performed on the modified intent-to-treat population (see Section 11.5 for definition of this population). A simple Bonferroni adjustment will be made to allow for the two active groups each being compared to placebo. This is a conservative approximation to two-sided Dunnett's test for multiple comparison to control in a general linear model. [CHAPMAN, 1993] An overall alpha level of 5% will be used i.e. an alpha for each of the two comparisons to placebo of 2.5%.

### **11.2.2. Other Comparisons of Interest**

The primary comparison described above will also be performed using the evaluable population (see Section 11.5). The analyses of carotid plaque Lp-PLA2 activity will be repeated for carotid plaque Lp-PLA2 mass. Details for all other formal comparisons of interest are given in Section 11.7.2 and Section 11.7.3.

### **11.3. Interim Analysis**

None planned.

#### **11.4.2. Sample Size Sensitivity**

Sample size sensitivity for this study is shown in Table 2 below based on 27 modified intent-to-treat patients and a range of clinically relevant inhibitions and between-subject standard deviations on the log-scale:

**Table 2 Statistical power (%) for 27 patients per group**

| Between-subject standard deviation on log-scale | Clinically relevant level of inhibition |     |      |
|-------------------------------------------------|-----------------------------------------|-----|------|
|                                                 | 40%                                     | 50% | 60%  |
| 0.6                                             | 79%                                     | 97% | >99% |
| 0.7                                             | 65%                                     | 90% | 99%  |
| 0.8                                             | 52%                                     | 81% | 97%  |

For a clinically relevant inhibition of 50% and between-subject standard deviation on the log scale of 0.7 if there are 21 modified intent-to-treat patients the power is 81%, while if there are 24 modified intent-to-treat patients the power is 86%.

#### 11.4.3. Sample Size Re-Estimation

No sample size re-estimation will be performed within this study. However if final results from study SB-480848/021 show significantly different variability from those seen at the interim analysis then the power and sample size of this study will be re-assessed.

### 11.5. Analysis Populations

The populations to be evaluated are:

- modified intent-to-treat: patients receiving at least one-dose of study medication and having valid Lp-PLA2 activity data from carotid plaque.
- intent-to-treat: patients receiving at least one-dose of study medication and having at least one efficacy assessment post-randomisation
- evaluable: subset of modified intent-to-treat population of patients who have at least 10 days of study medication, are between 80 and 120% compliant with medication, as defined in Section 11.6.3, and have carotid endarterectomy surgery within 24 hours of last dose of study medication.
- safety: patients receiving at least one dose of study medication.

For efficacy, the modified intent-to-treat population is of primary interest. The primary analysis will be repeated in the evaluable patient population as a sensitivity check. If the analyses are consistent then all plaque efficacy analyses will be performed on the modified intent-to-treat population only. If the analyses are inconsistent then data from non-evaluable patients will be reviewed in detail to identify the reason for the discrepancy, if possible. Unless a reason for discrepancy is apparent other analyses will be repeated in both populations. For plasma efficacy analyses the dropout rate and possible relation of the dropout pattern to treatment group will be assessed. If appropriate, plasma efficacy analyses may be repeated for the intent-to-treat population.

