**4. STUDY DESIGN**

A multi-centre, randomised, double-blind, placebo controlled, parallel group study in patients with documented carotid artery disease requiring surgery.

Male or female patients (post-menopausal or using adequate contraception), 35 years of age or above, with planned carotid endarterectomy will be eligible for the study.

Patients will be required to attend the hospital as an out-patient approximately 4 times for study-related procedures. Additionally, study procedures will be conducted on 3 occasions during a patient's planned hospital stay for carotid endarterectomy.

The study consists of 3 parts:

1. **Screen** - at Visit 1, written, informed consent and eligibility assessments will be performed [to be completed in a maximum of 4 weeks prior to randomisation (Visit 2)].
2. **Baseline, Study medication** - baseline assessments and randomisation to one of 2 treatment groups or matching placebo, will occur at Visit 2. At randomisation, patients will be stratified according to statin use and gender. The study medication period is 14 (+/-4) days. Patients will attend one outpatient visit during the 2-week study medication period (Visit 3) and will be telephoned on treatment day 14 if they are to take study medication for longer than 14 days.
3. **Follow-up** - the end of the study medication period will coincide with planned carotid endarterectomy. The last dose of study medication will be taken once a patient has been admitted to hospital during the day prior to surgery, for the purposes of PK and PD sampling (Visit 4). Carotid endarterectomy will take place the next day (Visit 5) according to local institution surgical guidelines. Final PK/PD samples will be taken during the day following surgery (Visit 6). A follow-up visit will occur 2 weeks after the end of study medication (Visit 7).

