### **6. STUDY ASSESSMENTS AND PROCEDURES**

A Time and Events Table is shown in Appendix 1.

Screening procedures should be conducted over a maximum period of 4 weeks prior to Visit 2 (baseline/randomisation).

The visit window for weekly visits is +/- 2 days. Study medication should be taken for 14(+/- 4) days. Visit 5 (day of surgery) must be conducted on the day following the last dose of study medication. Visit 6 must be conducted on the day after surgery, ie. 2 days following the last dose of study medication.

Visit 7 (follow-up) should be conducted 14 days (+/- 3 days) following the last dose of study medication.

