**Table 1 PK/PD Sampling Schedule**

| Sampling Times                 | Rationale             | Visit 4 
Day prior to
surgery
(after
admission) | Visit 6
Day after
surgery |
|--------------------------------|-----------------------|-------------------------------------------------------------------------|---------------------------------|
| Just before dose               | Trough Conc.          | X                                                                       | —                               |
| 0.5-2 h after dose             | Absorption
Phase   | X                                                                       | —                               |
| 2.5-4 h after dose             | Peak Conc.            | X                                                                       | —                               |
| 6-12 h after dose              | Distribution
Phase | X                                                                       | —                               |
| Any time prior to
discharge | Elimination
Phase  | —                                                                       | X                               |

1. if hospital practice does not allow PK/PD sampling to occur at the specified timepoints during Visit 4, where possible the sampling should be incorporated into the previous visit (3) when study medication is taken in clinic.

Visit 4 can be conducted by telephone, provided PK sampling has been carried out at V3. Patients not attending the Hospital for V4 will be telephoned to confirm that the subject will take their last dose of study medication with food in the morning of visit 4 (the day immediately prior to surgery). The patient should be reminded that Visit 5 is a fasting visit and the patient must not eat or drink with the exception of water, after 11pm on visit 4.

Patients attending the Hospital for visit 4, will be instructed not to take their dose of study medication until after admission to hospital.

The first PK and PD (Lp-PLA2) blood sample at Visit 4 will be collected just before taking study medication. The time of dosing and sample collection will be recorded in the CRF and samples taken within the following time windows:

- 0.5 - 2 hours post dose
- 2.5 - 4 hours post dose
- 6 - 12 hours post dose

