### **7.2. Dosage and Administration**

At Visit 2, patients will be randomised to one of three dose groups:

- SB-480848 40mg
- SB-480848 80mg
- Matching placebo

Patients will be provided with 2 bottles and will take 2 tablets from each bottle per day. Patients will continue with their allocated dose group for the 14+/-4 day treatment period.

Study medication should be taken in the morning with food. If PK/PD assessments are to be made during Visit 4 (Day Prior to Surgery) patients should delay taking study medication until instructed to do so after admission to hospital.

On fasting visit days, morning doses of study medication will be taken in the clinic after all fasting laboratory specimens have been obtained.

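### The evaluable population's 24-hour limit does not match the calendar-day schedule, so an unknown share of adherent patients could drop out of the sensitivity analysis

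*Protocol*

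**What the plan says.** Section 11.5 builds the evaluable population from the modified intent-to-treat population. It requires at least 10 days of medication, compliance between 80 and 120%, and that patients "have carotid endarterectomy surgery within 24 hours of last dose of study medication". Its role is stated there: "The primary analysis will be repeated in the evaluable patient population as a sensitivity check". If the two analyses disagree, data from non-evaluable patients are reviewed in detail, and unless a reason emerges other analyses are repeated in both populations.

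Elsewhere the protocol counts days. Section 6 states "Visit 5 (day of surgery) must be conducted on the day following the last dose of study medication". Section 6.3.1.1 and note 1 of Appendix 1 likewise place the last dose on the day before surgery, with no limit in hours.

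On time of day, the general rule in Section 7.2 is "Study medication should be taken in the morning with food". Two routes then apply to the last dose:

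- **Visit 4 by telephone** (text under Table 1): the call confirms that "the subject will take their last dose of study medication with food in the morning of visit 4".
- **Visit 4 in hospital** (Sections 4 and 7.2): "The last dose of study medication will be taken once a patient has been admitted to hospital during the day prior to surgery", and for PK/PD sampling "patients should delay taking study medication until instructed to do so after admission to hospital". No hour is given.

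The hour of surgery is left to local practice.

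**The concern.** A limit of 24 clock hours and a rule of one calendar day are different conditions. When the dose is given on one day and surgery follows on the next, the interval is at most 24 hours only if surgery starts no later in the day than the dose did. A patient dosed at 08:00 and operated on at 10:00 the next day has met every scheduling instruction, yet is non-evaluable.

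An evaluable population is meant to remove patients whose conduct departed from the plan. Here it would also remove adherent patients according to their theatre slot. The sensitivity check on the primary endpoint would then be smaller and less representative than intended. Lost precision alone could make it look inconsistent with the primary result and set off the review in Section 11.5.

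**Working it through.** **1. The plan's own figure.** Inputs from Sections 11.1 and 11.4.1: difference ln 2 = 0.693, SD 0.7 on the log scale, two-sided alpha 0.025 per comparison, 90% power. For a two-sample t-test the noncentrality is 0.693 / (0.7 × √(2/n)). At n = 27 this is 0.693 / 0.1905 = 3.64, giving power 90.5%; at n = 26 power is 89.2%. So 27 per group is reproduced. The same formula returns Table 2 and the stated 81% (n = 21) and 86% (n = 24). The protocol gives no expected size for the evaluable population.

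**2. The interval.** Hours from last dose to surgery = 24 + (clock time of surgery − clock time of dose). The patient is excluded when surgery is later in the day than the dose.

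**3. The excluded share.** The protocol supplies neither clock time, so these are assumptions: dose and surgery times independent and uniform over the ranges shown.

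| Assumed dose time | Surgery 08:00-12:00 | Surgery 08:00-16:00 | Surgery 13:00-16:00 |
|---|---|---|---|
| 07:00-09:00 | 94% | 97% | 100% |
| 07:00-10:00 | 83% | 92% | 100% |
| 09:00-12:00 (after admission) | 38% | 69% | 100% |
| 10:00-14:00 (after admission) | 12% | 50% | 96% |

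One cell by hand: for a dose at 07:00-10:00 and surgery at 08:00-16:00, the probability that surgery is earlier in the day than the dose is the integral of (d − 8)/8 × 1/3 over d from 8 to 10, which is 2/24 = 8.3%. So 91.7% are excluded.

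**4. Effect on the sensitivity comparison.** As an illustration, start from 27 per arm (the modified intent-to-treat number) and ignore the other two evaluability criteria. Effect and SD are as in step 1.

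| Left per arm | Power |
|---|---|
| 27 | 90% |
| 24 | 86% |
| 20 | 78% |
| 14 | 60% |
| 7 | 28% |

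At 14 per arm the standard error of the difference rises from 0.7 × √(2/27) = 0.191 to 0.7 × √(2/14) = 0.265, a factor of √(27/14) = 1.39.

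**The case against.** **Most adherent patients are excluded.** A reader might infer this from the morning-dosing rule. The documents do not support it. No clock time is given for either event, and the explicit instruction for a morning last dose covers only patients who do not attend hospital for Visit 4. Those who attend wait until after admission. Some text suggests an early dose there too: the pre-dose sample is fasting (Section 6.3.2.1), a sample is due 6-12 hours after the dose (Table 1), and patients who cannot arrive early may be sampled at Visit 3. None of this fixes an hour. With a dose at 10:00-14:00 and surgery at 08:00-12:00, only about 12% are lost.

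**The trial's conclusion is at risk.** This does not follow either. The modified intent-to-treat population is primary, so the primary test, its alpha and its sample size are untouched. Theatre slot should not depend on arm in a randomised, double-blind trial, so no between-arm bias is shown. With a half-life of 25-45 hours, a few hours beyond 24 need not change the effect much. Repeat analyses follow only if the review finds no reason, and a timing exclusion would be easy to spot.

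**24 hours may simply mean the next day.** Sections 1.3 and 7.3 describe trough inhibition as 24 hours post-dose, which fits a nominal one-day reading, and Section 11.6.5 lets the Reporting and Analysis Plan describe deviations. This is plausible, but the criterion as written is in hours, and applied literally it removes adherent patients. The mismatch stands; the stronger readings do not.

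**Conclusion.** The mismatch between Section 11.5 and the schedule is in the text and needs no assumption. Its size does: across the assumed uniform times the excluded share runs from about 12% to 100%, being 83-97% for an early-morning dose with surgery at 08:00-12:00 or 08:00-16:00, and 12-50% for a 10:00-14:00 dose with the same surgery times. The harm is confined to the sensitivity check. It loses precision and representativeness, and could appear to disagree with the primary analysis for that reason alone. The power figures are illustrative, because 27 is not a target for the evaluable set. This is a minor to moderate point, worth settling because the choice decides who enters the sensitivity analysis.

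**What to change.** Before unblinding, reconcile the third evaluability criterion in Section 11.5 with the Visit 5 rule in Section 6 by defining it as surgery on the calendar day after the last dose of study medication. This changes one phrase in an analysis-set definition and alters no dosing or surgical instruction.

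Adjusting for the dose-to-excision interval should not be added unless both times are recorded for every patient, and the protocol does not say that they are. Dosing time is mentioned only with PK/PD sampling under Table 1, and Section 8.1 asks only for the date of anaesthetic drugs. Collecting both times could need new case report form fields.
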